## **11.0 TOXICITIES/SIDE EFFECTS**

FOLFOX and 5-FU are FDA-approved, and are used as part of standard treatment in the US for patients with locally advanced rectal cancer. Therefore, all clinicians recruiting study subjects have considerable experience with this regimen. The toxicity of each specific agent is outlined below. The regimen used in this clinical trial also represents the standard care for patients with locally advanced rectal cancer.

### **11.1 Anticipated Toxicities – Oxaliplatin**

Likely:

- Inflammation of the nerves, resulting in numbness, tingling, etc.
- Numbness and tingling when touching items that are cold (neuropathy)
- Loss of strength and energy
- Nausea
- Decreased production of red blood cells, possibly requiring transfusion

Less Likely:

- Diarrhea
- Loss of appetite
- Fever
- Coughing
- Vomiting
- Pain
- Back pain
- Constipation
- Headache
- Dizziness
- Difficulty sleeping
- Abdominal pain
- Inflammation of the mouth
- Feeling of tightness in the chest
- Fluid retention and swelling
- Reactions at injection site
- Runny nose and watery eyes
- Bone and joint pain
- Upper respiratory infection
- Abnormal limb stiffness
- Decreased production of white blood cells, possibly causing infection
- Decreased number of platelets, possibly causing bleeding
- Elevated liver function tests

Rare, but serious:

- Blood clots
- Dehydration
- Nose bleeds

- Rash
- Allergic reaction
- Chest pain
- Low blood potassium
- Acid reflux
- Changes in taste perception
- Redness and pain in the skin of the hands and feet (hand-foot syndrome)
- Reddening of the face
- Inflammation of the throat
- Hair loss (reversible)
- Difficulty urinating
- Increased tearing (eyes)

The Sanofi scale, developed to grade sensory neuropathies, will be used to evaluate oxaliplatin-associated sensory neuropathies.

| Toxicity Scale for the Sensory Neuropathies Associated with Oxaliplatin |                                                                                                   |
|--------------------------------------------------------------------------------|---------------------------------------------------------------------------------------------------|
| Grade                                                                   | Symptoms                                                                                   |
| Grade 0                                                                        | None                                                                                              |
| Grade 1                                                                        | Paresthesias/dysesthesias* of short duration that resolve and do not interfere with function.     |
| Grade 2                                                                        | Paresthesias/dysesthesias* interfering with function, but not in activities of daily living (ADL) |
| Grade 3                                                                        | Paresthesias/dysesthesias* with pain or with functional impairment that also interfere with ADL.  |
| Grade 4                                                                        | Persistent paresthesias/dysesthesias* that are disabling or life threatening.                     |
| * May be cold-induced.                                                         |                                                                                                   |

| Comparison of the Symptoms and Treatment of Pharyngo-Laryngodysesthesias and Platinum Hypersensitivity Reactions |                                                                                                                 |                                                                                        |
|-------------------------------------------------------------------------------------------------------------------------|-----------------------------------------------------------------------------------------------------------------|----------------------------------------------------------------------------------------|
| Clinical Symptoms                                                                                                | Pharyngo-Laryngeal Dysesthesias                                                                          | Platinum Hypersensitivity                                                       |
| Dyspnea                                                                                                                 | present                                                                                                         | present                                                                                |
| Bronchospasm                                                                                                            | absent                                                                                                          | present                                                                                |
| Laryngospasm                                                                                                            | absent                                                                                                          | present                                                                                |
| Anxiety                                                                                                                 | present                                                                                                         | present                                                                                |
| O2 saturation                                                                                                           | normal                                                                                                          | decreased                                                                              |
| Difficulty swallowing                                                                                                   | present (loss of sensation)                                                                                     | absent                                                                                 |
| Pruritus                                                                                                                | absent                                                                                                          | present                                                                                |
| Urticaria/rash                                                                                                          | absent                                                                                                          | present                                                                                |
| Cold-induced symptoms                                                                                                   | yes                                                                                                             | no                                                                                     |
| BP                                                                                                                      | normal or increased                                                                                             | normal or decreased                                                                    |
| Treatment                                                                                                               | anxiolytics, observation in a controlled clinical setting until symptoms abate or at the physician's discretion | Oxygen, steroid, epinephrine, bronchodilators; fluids and vasopressors, if appropriate |

Neutropenia has been reported in 73% of patients receiving oxaliplatin with 5-FU and Leucovorin (44% grade 3 or 4). Grade 3 or 4 thrombocytopenia is reported to occur in 4% of patients receiving the combination.

## **11.2 Anticipated Toxicities – 5-fluorouracil**

Likely:

- Darkening of the skin and nail beds, dry, flaky skin
- Decreased red blood cells (anemia), the oxygen carrying cells, which could make you feel tired
- Decreased white blood cells (leukopenia), the infection-fighting cells, which could put you at risk for infection
- Nausea
- Vomiting
- Sores in mouth or on lips
- Thinning hair
- Diarrhea
- Brittle nails
- Increased sensitivity to sun

Less likely:

- Darkening and stiffening of the vein used for giving the drug
- Headache
- Weakness
- Muscle aches
- Heartburn (for which you could be given other medication)
- Nausea and vomiting (for which you could be given other medication)
- Loss of appetite
- Hair loss, which is expected to be temporary. Hair is expected to grow back after chemotherapy is stopped.
- Skin irritation, itchy skin rash (for which you could be given skin medication)
- Hand-foot syndrome--characterized by numbness, tingling and painful blistering on the palms of hands or soles of the feet. Usually temporary, but some may be long-lasting. These may be made worse by exposure to cold temperature and cold objects. These effects can be minimized by avoiding exposure to cold (including not drinking cold beverages) for up to 5 days after your infusion.)

Rare but serious:

- Difficulty walking
- Irritation of the eyes
- Increased tearing of eyes
- Blurred vision
- Low blood pressure (for which you could be given other medication)
- Chest pain (You will be evaluated by your doctor to determine the cause. If angina (chest pain) is presented it can be temporary with treatment, but can in the short term lead to a life-threatening heart attack)
- Changes in tests that measure heart rhythms (Temporary side effect; observed and use heart medications for control)
- Decrease in the bone marrow function. Low white blood counts increase the risk of infection and might require antibiotics and possibly hospitalization. Low red blood counts (anemia) would make you feel tired and might require transfusions. Low platelet counts increase the risk of bruising and bleeding and might require transfusions.

## **11.3 Anticipated Toxicities – Leucovorin**

Side effects are uncommon, and are associated with prolonged use. These include an allergic reaction, with symptoms such as skin rash, hives, and itching, and/or breathing problems such as wheezing. Medicines are available to help you if these should occur. Although these side effects are extremely rare, anaphylactic reactions can be serious and are potentially fatal. Leucovorin may interfere with the effects of anti-seizure medications such as phenobarbital, phenytoin, and primidone. When leucovorin is given together with 5-FU, side effects may increase.

#### **11.4 Anticipated toxicities - Capecitabine (Xeloda®)**

Likely:

- Diarrhea or loose stools
- Inflammation and/or painful sores in the mouth that may make swallowing difficult (mucositis)
- Nausea
- Redness or sores on palms of the hands or soles of the feet (palmar-plantar erysdyesthesia, or “hand-foot syndrome”)
- Dry skin (xerosis)
- Itching sensation (pruritus)

Less likely:

- Decreased red blood cells (anemia), the oxygen carrying cells, which could make you feel tired
- Decreased white blood cells (leukopenia), the infection-fighting cells, which could put you at risk for infection
- Decreased number of platelets (thrombocytopenia), the blood-clotting cells, which could put you at increased risk of bleeding
- Vomiting
- Stomach or abdominal pain
- Loss of appetite, not eating (anorexia)
- Constipation
- Heartburn
- Fatigue
- Generalized weakness and loss of strength
- Hair loss
- Rash
- Red, sore eyes
- Fever
- Sensation of light-headedness or vertigo (dizziness or spinning sensation)
- Headache
- Pain, including joint, muscle, or bone pain
- Infection

Rare but serious:

- Blood clots and/or bleeding
- Dehydration
- Abnormal liver function tests
- Heart attack
- Abnormal heartbeat

#### **11.5 Anticipated Toxicity – Radiotherapy**

Expected acute side effects of radiation therapy include:

- Abdominal cramping
- Diarrhea
- Skin erythema
- Dysuria
- Tenesmus
- Leukopenia
- Lymphopenia
- Thrombocytopenia

Late effects of radiation therapy include:

- Increased frequency of bowel movements
- Bowel urgency
- Infertility in women who have not undergone an ovarian transposition
- Early menopause in pre-menopausal women who have not undergone an ovarian transposition
- Vaginal dryness and narrowing

## **11.6 Surgical Complications**

Surgery is part of the standard treatment of most patients with rectal cancer. The most common complications of surgery for rectal cancer include wound infection, pelvic infection, bleeding, bowel obstruction, vein thrombosis, pneumonia, cardiac arrhythmia, and heart attack. Long-term side effects include frequent bowel movements, urinary problems, sexual dysfunction, and hernia. Surgical complications will be graded by the treating surgeon according to the Clavien-Dindo classification of surgical complications. [88] Refer to Appendix N.

## **11.7 Dosage Modifications Based on Adverse Events**

### **11.7.1 Dose Modifications for Radiotherapy**

Uninterrupted treatment is planned. Treatment may be interrupted for acute toxicity. Radiation therapy will be held on any planned treatment day in which the patient exhibits Grade 3 toxicity, unless such toxicity cannot be reasonably attributed to pelvic radiation (i.e., stomatitis or hand-foot syndrome). Radiation will be held until the toxicity resolves to less than Grade 2, at which point radiation will be resumed. If radiation treatment is held, then chemotherapy should also be held. A toxicity which delays planned radiation therapy for greater than 2 weeks will be adjudicated as dose-limiting toxicity for the purposes of this trial. The patient will be examined at least once a week, or as indicated by the treating physician, during the course of radiation. CBC and platelets will be drawn weekly or as indicated at the discretion of the treating physician. RT interruption is to be minimized, and is allowed only for regional symptoms.

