In addition, we will calculate therapy compliance using the following measures: the number of days RT was held, the number of RT delays of  $\geq 1$  week, the number of dose delays and the number of dose reductions in INCT and CNCT. We will also calculate the rate of select hematologic events (as outlined in 17.2), select non-hematologic events (as outlined in 16.0), and unexpected Grade 3 or higher non-hematologic adverse events and surgical complications in each treatment arm. Comparisons will be done using the Wilcoxon Rank Sum test or the Fisher’s Exact test.

**14.3 Secondary objective 2.:** *To measure patient-reported functional outcomes and QoL in patients with LARC treated with NCT, CRT and NOM, and compare these to patients treated with TME.*

The primary analyses for this aim will use data combined across both treatment arms; however, differences according to treatment will also be investigated. The primary endpoint will be QoL as measured one year from the end of TNT. Secondary endpoints will be bowel, sexual, and bladder function. While the subscales will be reported, the primary secondary endpoints will be the total scores on the BFI, FSFI and IIEF. With a total of 325 patients accrued, we expect that 129 patients will obtain complete clinical response and 196 will undergo TME. Approximately 15 to 30 patients initially treated with NOM are expected to cross over to TME at some point during follow-up. For the primary analyses, the NOM group will include these cross-overs on an intent-to-treat analysis. In secondary analysis, patients who eventually crossed over to receive surgery will be included in the TME group. We define this analysis as a comparison between TME vs. durable NOM. Durable NOM is defined as 3-year disease-free survival. We expect that 70% of patients will complete the QoL assessment at 1 year. This response rate takes into account refusals to complete the QoL

questionnaires, and the approximately 20% of patients who will develop distant disease or die before the 1-year time point. Thus, at 1 year we expect to have information on 94 TME patients and 62 NOM patients.

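### Section 11.7.1 gives opposite radiotherapy-hold instructions for Grade 3 toxicity that is attributable to radiation but is not a regional symptom, chiefly cytopenia

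*Protocol*

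**What the plan says.** Section 11.7.1 of the protocol contains three statements on interrupting RT.

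- A permissive one, with no limit by grade or region: "Treatment may be interrupted for acute toxicity".
- A mandatory one: "Radiation therapy will be held on any planned treatment day in which the patient exhibits Grade 3 toxicity". Its only exemption reads "unless such toxicity cannot be reasonably attributed to pelvic radiation (i.e., stomatitis or hand-foot syndrome"). The hold lasts until the toxicity is below Grade 2, and chemotherapy is to be held with it.
- A restrictive one, which closes the paragraph: "RT interruption is to be minimized, and is allowed only for regional symptoms".

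The paragraph also provides for blood counts during RT: "CBC and platelets will be drawn weekly or as indicated at the discretion of the treating physician".

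Section 11.5, under the words "Expected acute side effects of radiation therapy include", lists eight effects: abdominal cramping, diarrhea, skin erythema, dysuria, tenesmus, leukopenia, lymphopenia and thrombocytopenia.

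Section 11.7.2, on chemotherapy doses including 5-FU and capecitabine during radiation, adds that when chemotherapy is held, RT may continue if the physician so decides.

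Section 14.2 uses "the number of days RT was held" and the number of RT delays of one week or more as two of its four compliance measures. It compares the arms by Wilcoxon rank sum or Fisher's exact test and describes the compliance and adverse-event objectives as exploratory.

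**The concern.** A site needs one answer to a simple question: does a Grade 3 cytopenia attributed to pelvic RT, in a patient without local symptoms, stop RT? The mandatory sentence says it does. The closing sentence says it may not. Whichever one a site follows, it departs from the other, although section 16.1.1 has sites audited for protocol compliance.

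Two things are at stake. Patients with the same blood count may be handled differently from site to site. And the recorded hold days and RT delays then depend partly on how the paragraph was read, so they measure compliance less cleanly.

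**Working it through.** No sample size, power or error rate is involved, and the plan gives no figure to reproduce. The check sets the sentences side by side.

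1. **Where the sentences agree.** Five of the eight acute effects in 11.5 are regional: cramping, diarrhea, skin erythema, dysuria and tenesmus. At Grade 3 the mandatory sentence requires a hold, and the closing sentence allows it. There is no conflict.

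2. **Where they disagree.** The remaining effects number 8 − 5 = 3: leukopenia, lymphopenia and thrombocytopenia. These are laboratory findings and not regional symptoms. Section 11.5 attributes them to RT, so a Grade 3 cytopenia put down to RT falls outside the exemption.

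| Sentence | Grade 3 cytopenia attributed to RT, no regional symptom |
|---|---|
| 11.7.1, mandatory hold | RT must be held |
| 11.7.1, closing sentence | RT may not be interrupted |
| 11.7.2, if chemotherapy is held | RT may continue, physician decides |

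3. **Whether precedence is stated.** It is not. Section 11.7.1 does not rank its sentences, and the 11.7.2 sentence refers to neither of them.

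4. **Whether the case will be seen.** Section 11.7.1 provides for blood counts weekly or as indicated, so such cytopenias can be detected during RT.

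5. **What reaches the data.** For one such patient, the mandatory sentence adds every day from the start of the hold until the toxicity falls below Grade 2 to the count of days held. The closing sentence adds 0. If the hold lasts a week or more, the patient also enters the 14.2 delay count under one reading and not under the other.

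6. **How many patients.** This cannot be computed. The protocol gives neither a rate nor a duration for Grade 3 cytopenia during RT. The 44% Grade 3 or 4 neutropenia quoted in section 11.1 is for oxaliplatin with 5-FU and leucovorin and does not describe the RT phase.

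7. **What is not reached.** The 3-year disease-free survival estimate in 14.1, the organ-preservation comparison and selection rule in 14.2, and the R1-resection stopping rule in 14.5 use neither hold days nor RT delays.

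**The case against.** The best defence is that the paragraph has a coherent reading. Both examples in the exemption, stomatitis and hand-foot syndrome, are non-regional, so the closing sentence may merely restate that only regional effects stop RT. This works for the five regional effects. It fails for the cytopenias, because 11.5 names them as effects of RT.

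A second defence is that section 11.7.2 leaves matters to the physician. Every patient on RT also receives 5-FU or capecitabine, and section 11 lists leukopenia as a toxicity of both. A cytopenia may therefore lead to a chemotherapy hold, after which RT is discretionary. That stands in part: the choice is not simply between a compulsory hold and a forbidden one. But it adds a third instruction and leaves the other two unreconciled. The broader discretion wording in 11.7.2 sits under a chemotherapy heading and introduces chemotherapy dose tables.

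A third defence is that the consequence for the analysis is small. That stands. The compliance comparison is exploratory, and randomization is stratified by institution in permuted blocks (section 15.2), so a site's reading applies to both of its arms.

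**Conclusion.** The contradiction is real and narrow. It concerns Grade 3 toxicity that is attributable to radiation and is not a regional symptom, which in the protocol's own list means three cytopenias out of eight acute effects. It leaves patient handling unsettled in a case the protocol expects, and it adds noise to two exploratory compliance measures. Severity is minor. The conclusion assumes only that a cytopenia is not a regional symptom and that 11.5 means what it says in attributing cytopenias to RT.

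A reader might infer more, and the documents do not support it:

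- **Bias between arms.** Arm 1 reaches RT after oxaliplatin-based chemotherapy and Arm 2 does not, so cytopenia during RT might differ. The protocol gives no rate to show this. Such a difference would be an effect of sequence, and with stratification by institution differing readings mainly blur it.
- **No hold for Grade 4.** The mandatory sentence names only Grade 3, but the permissive sentence has no grade limit, so interruption for Grade 4 is not barred by grade. This is a gap in drafting.
- **A clash over long delays.** A delay of more than 2 weeks "will be adjudicated as dose-limiting toxicity for the purposes of this trial", while 14.2 counts delays of at least 1 week. These are different quantities. The label enters none of the analyses in section 14, and the two thresholds do not contradict each other.
- **A count of affected patients.** Any such figure would rest on an assumed rate, with no duration to say which patients cross the one-week line.

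**What to change.** Rewrite section 11.7.1 so that the mandatory hold sentence and the closing sentence agree with each other, with the list in 11.5, and with the sentence in 11.7.2 on continuing RT when chemotherapy is held. One rule should cover radiation-attributable hematologic toxicity and state the grades to which it applies. Which rule that is remains a decision for the investigators.

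The cost is one paragraph of protocol text and a notice to sites. Sample size, endpoints and analyses stay as they are.
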